## Abstract

**Background:**

Barefoot locomotion has evoked an increasing scientific interest with a controversial debate about benefits and limitations of barefoot and simulated barefoot walking and running. While most current knowledge comes from cross sectional laboratory studies, the evolutionary perspective suggests the importance of investigating the long-term effects. Observing habitually barefoot populations could fill the current gap of missing high quality longitudinal studies. Therefore, the study described in this design paper aims to investigate the effects of being habitually barefoot on foot mechanics and motor performance of children and adolescents.

**Methods:**

This study has a cross-sectional, binational design and is part of the “Barefoot Locomotion for Individual Foot- and health Enhancement (Barefoot LIFE)” project. Two large cohorts (n_(total)_ = 520) of healthy children and adolescents between 6 and 18 years of age will be included respectively in Germany and South Africa. A barefoot questionnaire will be used to determine habitually barefoot individuals. The testing will be school-based and include foot mechanical (static arch height index, dynamic arch index, foot pliability) and motor performance (coordination, speed, leg power) outcomes. Gender, BMI and level of physical activity will be considered for confounding.

**Discussion:**

The strength of this study is the comparison of two large cohorts with different footwear habits to determine long-term effects of being habitually barefoot on foot mechanics and motor performance.

**Electronic supplementary material:**

The online version of this article (doi:10.1186/s13047-016-0166-1) contains supplementary material, which is available to authorized users.

## Background

The general interest in barefoot locomotion has increased and attracted a scientific focus for more than a decade. There is an ongoing debate on the advantages and disadvantages [1, 2] with most of the knowledge coming from cross-sectional laboratory or field studies [3–5].

Numerous studies show that acute barefoot walking or running change foot strike pattern from a rearfoot strike to a mid-or forefoot strike with subsequently more ankle plantar flexion at foot strike [6–8], decreased stride length and increased stride frequency [4, 6, 7], reduced ground reaction forces [3, 6, 7] and increased range of motion (ROM) in the midfoot and MTP joints [6]. While this emphasizes the evidence for short-term effects [3, 4], the influence of long-term (habitual) barefoot locomotion on biomechanics, motor performance and injuries remains unclear [[name], Heidt C, [name], [name], [name]. Long-term effects of habitual barefoot running and walking: a systematic review. Manuscript submitted for publication]. Few prospective studies which evaluated the effects of regular barefoot running interventions in habitually shod people reported no or controversial findings regarding relative injury rates [9], biomechanics [10] and running economy [11, 12].

Additionally, several cross-sectional studies have evaluated the effect of living habitually barefoot on foot posture and foot mechanics. A general consensus seems to be that habitually barefoot individuals have stronger feet and less foot and toe deformities [13–15]. The most evident difference to habitually shod individuals is that the foot of habitually barefoot individuals is wider in the forefoot region [16–18]. Furthermore, it is found that habitually barefoot feet have a higher arch [14, 15, 19], are more pliable [20] and have a reduced hallux angle [21]. However, there are several limitations to these studies that have to be mentioned. While some studies investigate habitually barefoot children [14, 15], other authors describe habitually barefoot adult populations [16, 17]. It is known that the foot and foot arch characteristics still develop during childhood and plateau in adolescence [22]. Furthermore, some of these studies are of low methodological quality [3]. Also, the differences between habitually barefoot and shod participants are not always clearly defined. And lastly, several studies use participants from different continents, ethnic backgrounds and possibly also socioeconomic backgrounds [16, 20], which influences the interpretation of the results. It has been shown that there are significant differences in foot morphology between different ethnicities and therefore ethnicity should be taken into account when assessing skeletal differences [23].

Although previous studies suggest differences in foot posture and foot mechanics between habitually barefoot and shod people, the clinical and practical relevance remain speculative. However, cross-sectional studies on short-term barefoot effects emphasize the hypothesis that regular locomotion with and without shoes influences motor performance of adults [5] and children [[name], Heidt C, [name], [name], [name]. Long-term effects of habitual barefoot running and walking: a systematic review. Manuscript submitted for publication]. In this context, one may speculate whether the magnitude of such effects may increase with age (and barefoot experience).

The aim of our study is to evaluate the effect of being habitually barefoot on foot mechanics and motor performance of children and adolescents between the ages of 6–18 years. Additionally, we will evaluate if differences between habitually barefoot and shod children are age-dependent. Based on current knowledge, we hypothesize that children growing up wearing shoes regularly, have lower arches compared to their barefoot counterparts. It is also anticipated that the habitually barefoot children perform better on the barefoot motor performance tasks than the habitually shod children.

## Methods/Design

This protocol is reported according to the SPIRIT statement for improved reporting of study protocols [24].

### Study design

This is a binational multicenter, cross-sectional observational study looking at differences of foot mechanics and motor performance between habitually barefoot and habitually shod children and adolescents aged 6–18 years. Ethical approval has been obtained from the ethics committee of the medical association Hamburg (protocol number PV4971) and Stellenbosch University ethics committee (protocol number HS1153/2014). The regional separation of the recruitment is due to the obligation of footwear use in most German educational institution while in South Africa the habit of being barefoot prevails.

### Participants

After pilot testing for reliability and validity of the measurement apparatus, recruitment of participants exclusively will take place in rural and urban primary and secondary schools with no restriction to school type. In South Africa, primary school attendees are aged 6–13/14 and secondary school children are between 13/14–18 years old, their German counterparts are 6–9/10 and 9/10–18. With approval from the German and South African supervisory school authorities, schools will be randomly selected per stratum (representing a combination of district and type of school) and contacted by the principal investigators. Schools (in blocks of five primary schools and five secondary schools) will be initially contacted via email and when interested visited by the study staff for further organisation. If the school wants to participate, consent forms for all pupils (and their parents) will be provided in the appropriate language (English, Afrikaans, Xhosa or German, Additional file 1). No limit will be set per school for maximum number of participating children per age. We will strive for an equal distribution of portion of participants per school to ensure equal representation. For participation, pupils will be requested to bring along the signed consent form on the testing day.

Inclusion criteria will consist of healthy children that are physically active for at least 120 accumulative minutes per week (parent reported). Children and young adolescents between the age of 6 and 18 will be recruited for this study. Exclusion criteria will be evaluated by parent proxy report and consist of current injuries of the lower extremity, abnormal gait or any neurological or neuromuscular abnormalities likely to influence the gait.

### Testing procedure

Methodological planning stipulates all anthropometrical, foot and motor performance measurements to be performed during a physical education lesson. Prior to the testing, a physical activity questionnaire for children/adolescent (PAQ-C and PAQ-A [25, 26]) and a barefoot questionnaire will be distributed by the teachers and collected by the study staff on the testing day and briefly checked for completeness. All children bringing the signed consent form and voluntarily want to participate will be gathered and all relevant information for the testing will be given by the principal investigator. After a short warm up period (jogging for < 5 min), participants will be randomly allocated to the seven testing stations:AnthropemetryFoot caliperPressure plate20 m sprintingLateral jumpingStanding long jumpBackwards balancing

After their first testing station, a participant will be transferred to the next vacant station without a fixed order. Testing station 1–3 will be completed only barefoot, while testing stations 4–7 will be performed in barefoot and shod conditions. The order of the condition is randomized a priori on the registration sheet which is distributed to the participants on the testing day. A flowchart displaying the participant flow through the study is shown in Fig. 1.

**Fig. 1 Fig1:**
[figure not shown]
A flowchart demonstrating the participant flow through the study

### Barefoot questionnaire

Participants will complete a six-item questionnaire used to decide if a child can be considered barefoot or shod. This questionnaire (Additional file 2) is developed specifically for this study and inquires if the child is barefoot on a three point Likert scale: most of the time, half of the time or barely/none of the time during 1) school 2) sports and 3) in and around the house. These questions will be asked twice: one for the warm weather and one for cold weather. For those in secondary school, questions are repeated for when they were in primary school. Due to the multi lingual culture of South Africa, the questions will be asked in Afrikaans, English and Xhosa. Children will be considered barefoot when they are always barefoot in and around the house and always barefoot in school *or* during sports -in warm weather- in primary school. In secondary school they have to have a similar level of barefootness during primary school *and* are always barefoot in and around the house currently.

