### Statistical analysis

Descriptive data will be presented using descriptive statistics. The participant’s barefoot questionnaire and the PAQ outcomes will be compared to all attending children in 2 primary (1 rural, 1 urban) and 2 secondary schools to assess external validity. The outcome measures will be evaluated for normality using Shapiro-Wilkins and visually using P-P plots, if possible, non-normal distributed data will be adjusted. Mixed Models linear regression will be used to assess if the foot mechanical and motor performance outcomes differ between the barefoot and the shod participants (fixed factors). Furthermore, we will test differences due to being barefoot or shod change by age by adding an interaction of age*group to the linear regression. Differences in foot strike pattern during jogging and sprinting between barefoot and shod participants will be assessed using ordinal regression. The school of a participant will be added to the model as a random effect in order to adjust for possible differences between the schools and their geographical location. Furthermore, Gender, BMI, PAQ-Score, ethnicity and inside/outside testing will be tested for confounding in all models (regression coefficient changes >10 %). We hypothesize that older boys could have higher arches (lower dAI) [37] and perform better on motor performance tasks, while girls’ feet will show a higher pliability. BMI increases the dAI and possibly decreases motor performance [38, 39]. A higher level of physical activity (higher PAQ score) is probably related to better motor performance. And lastly, Caucasians could have higher arches (lower dAI) [40].

We anticipate that gender might modify the effect of being barefoot or shod on the outcome measures and therefore gender will additionally tested as an effect modifier (interaction between outcome and gender *p* < 0.1). In all cases, a significance level of 5 % is pre-stipulated.

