### Barefoot questionnaire

In designing the study, decisions have been made that could influence the outcome and its interpretations. The level of barefootness of the participants in South Africa is one of those decisions since the current literature descriptions are diverse and even ambiguous at times.

Some studies use a percentage of yearly mileage [8, 9] or running time [41] to define a habitually barefoot person. Other studies define a habitually barefoot individual as being barefoot for all life [8, 14, 16, 20] or as living in an area where it is common to be barefoot [15, 19, 21]. Children in Germany are shod most of the time due to the climate and the culture of wearing shoes when outside. In South Africa a culture exists for children of being barefoot outside, and for younger children, even during sports and at school. Furthermore, the warmer climate allows the children to do so for the biggest part of the year. To distinguish between children who are habitually barefoot, a barefoot questionnaire has been developed. Participants in primary school (age range 6–12 years) are defined as habitually barefoot when they are always barefoot in and around the house as well as at school or during sports when it is warm. In secondary school being habitually barefoot is defined as always being barefoot in and around the house and having had the level of barefootness at primary school as previously described. The distinction between primary and secondary school was made because all secondary schools require wearing a uniform that includes wearing shoes and participation in most sports do as well. Therefore, it wasn’t feasible to include participants after the age of 13 years who had a similar level of barefootness as their counterparts in primary school.

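### The definition of habitually barefoot changes at secondary school, so the single age-by-group interaction over ages 6–18 mixes age with reduced barefoot exposure

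*Protocol article*

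**What the plan says.** **Primary school (Methods/Design, Barefoot questionnaire).** "Children will be considered barefoot when they are always barefoot in and around the house and always barefoot in school", with sport allowed as the alternative to school, in warm weather. This is current exposure.

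**Secondary school (same section).** "In secondary school they have to have a similar level of barefootness during primary school", and they must be pupils who "are always barefoot in and around the house currently". The school and sport part is met by recall of primary school. Only the home part is current.

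**Reason given (Discussion, Barefoot questionnaire).** "all secondary schools require wearing a uniform that includes wearing shoes and participation in most sports do as well". The authors conclude that it was not "feasible to include participants after the age of 13 years who had a similar level of barefootness as their counterparts in primary school".

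**Where the rule changes (Participants).** In South Africa, "primary school attendees are aged 6–13/14 and secondary school children are between 13/14–18 years old". The Discussion gives the primary range as 6–12 years, so the switch falls at 13 or 14.

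**The aim (Background).** "Additionally, we will evaluate if differences between habitually barefoot and shod children are age-dependent".

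**The test (Statistical analysis).** "we will test differences due to being barefoot or shod change by age by adding an interaction of age*group to the linear regression". School enters as a random effect. Gender, BMI, PAQ score, ethnicity and inside/outside testing are checked as confounders. School stage and current exposure are not among them.

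**The concern.** One label covers two exposures, and the age of the child largely decides which applies. Study design and the Discussion both make South Africa the expected source of barefoot children. There, younger barefoot children are barefoot at home and at school or in sport. Older ones had that history but need only be barefoot at home today, and the article says that shoes are compulsory at their schools and in most sports.

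The interaction is meant to show whether the barefoot–shod difference depends on age. If part of the effect fades once shoes are worn for school and sport, the interaction would show an effect that shrinks with age. If the effect really grows with age and barefoot experience, as the Background speculates, the loss of exposure could hide that growth. The plan as written allows either wrong conclusion. The main barefoot effect over 6–18 also becomes an average over two kinds of exposure.

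**Working it through.** **Inputs from the protocol article**
- Ages 6–18 (13 ages), 20 children per age per country. Check: 20 × 13 × 2 = 520, the stated total. The article gives no figure for the interaction itself.
- Dynamic arch index (dAI): important difference 0.038, SD 0.065 (printed 0065, read as 0,065).
- Switch of definition at 13 or 14.

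**Assumptions, not in the documents**
- A fraction r of the barefoot effect remains after the switch, which acts as an immediate step.
- Age enters linearly.
- There are 20 barefoot and 20 shod children at each age, as if country and group coincided.
- The school random effect is left out.

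**1. Overlap of age and definition.** Over the 13 ages, linear age and an indicator for the secondary rule correlate at 0.85 (switch at 14) or 0.87 (switch at 13).

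**2. Spurious slope when the true effect is constant.** Mean age is 12 and Sxx = Σ(age − 12)² = 182. Σ(age − 12) is −20 over ages 6–13 and +20 over ages 14–18. With effect 1 before the switch and r after it:

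slope = (−20 + 20r)/182 = −20(1 − r)/182 per year.

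- r = 0.75: −5/182 = −0.027 per year; × 12 years = −0.33, a decline of 33% of the effect.
- r = 0.5: −10/182 = −0.055 per year; × 12 = −0.66, or 66%.
- r = 1: no distortion.

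**3. False-positive rate on the dAI scale.** The standard error (SE) of the interaction slope is 0.065 × √(2/(20 × 182)) = 0.00152 per year. With a constant true effect of 0.038, a two-sided 5% test rejects as follows:

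| r | switch at 14 | switch at 13 |
|---|---|---|
| 1 | 5% | 5% |
| 0.75 | 11% | 11% |
| 0.5 | 28% | 30% |
| 0.25 | 54% | 58% |
| 0 | 78% | 82% |

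**4. Masking of a true increase.** Let the effect double from 0.038 at age 6 to 0.076 at age 18. The true slope is 0.038/12 = 0.00317 per year, and power with unchanged exposure is 55%. With the switch at 14, the weighted sum Σ(age − 12)(1 + (age − 6)/12) over ages 14–18 is 37.5, so

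expected slope = 0.00317 − (1 − r) × 0.038 × 37.5/182 = 0.00317 − 0.00783(1 − r).

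- r = 0.75: 0.0012; power 12% (11% with the switch at 13).
- r = 0.5: −0.0007; the sign is reversed.

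**5. Precision within one definition.** For ages 6–12, Sxx = 28 and SE = 0.065 × √(2/(20 × 28)) = 0.0039, which is √(182/28) = 2.5 times the full-range value. This uses 7 × 40 = 280 of the 520 children. Power for the increase in step 4 is 13%, against 55% over the full range with unchanged exposure. For ages 14–18, Sxx = 10 and the SE ratio is √(182/10) = 4.3.

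**The case against.** The best defence is that the rule is disclosed, reasoned and coherent under one reading. The Discussion names the level of barefootness among decisions that could influence the outcome and its interpretation, and explains why secondary pupils are treated differently. The study is about long-term effects. If the exposure is a barefoot upbringing, the interaction asks whether its effect persists. This stands in part: the choice is deliberate, and a reader who took it for a coding slip would be wrong. But the aim is worded as the effect of being habitually barefoot, primary pupils are classed on current habit, and nothing links the changed definition to the interaction test.

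The size is also open to challenge. The retained fraction is assumed, and at r = 1 nothing is distorted. The article does not say whether age is linear or categorical. With categorical age a step at 13/14 would be visible, but it still could not be assigned to age or to exposure. Because the two stages attend different schools, the school random effect might absorb part of the step. How much depends on between-school variance, which is not given, and the term is not designed to separate the two.

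Three stronger readings are tempting but unsupported:
- That the study cannot answer the age question at all. This holds for the pooled 6–18 test, not for the data: primary pupils share one definition, and the questionnaire records current and past exposure.
- That no child after 13 has primary-level exposure. The article says that including such children was not feasible. The primary rule accepts school or sport, and only most sports require shoes.
- That secondary barefoot pupils are simply formerly barefoot. They must still always be barefoot at home.

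**Conclusion.** The concern holds for the pooled interaction. The definition changes at a nearly fixed age in the expected barefoot group, the article itself says exposure could not be kept equal, and the planned model has no term for the change. The 6–18 interaction therefore reflects age and changed exposure together. That some distortion arises needs only r below 1; its size depends on r and on the simplifications in the working. Under them, the spurious decline is 33% of a constant effect at r = 0.75 and 66% at r = 0.5, and a true doubling with age is largely hidden at r = 0.75. These figures illustrate what could happen and do not predict it.

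This is a should-fix. Age dependence is an additional aim, the definition is disclosed, and the items needed for a better analysis are already collected. Left alone, the plan lets a change of exposure be reported as an effect of age.

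**What to change.** Keep the 6–18 interaction and add the following to the analysis:

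1. Estimate the barefoot–shod difference and its age trend separately under the primary rule and the secondary rule. Label the secondary group for what it is, for example: barefoot in primary school, currently barefoot at home only.
2. Use the current and past school and sport items to describe the exposure of each group. Any secondary pupils who still meet the primary rule can then be identified.
3. State that the pooled interaction reflects age and changed exposure together, and draw conclusions on age dependence only from the analysis within one definition.

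Splitting exposure into categories inside one pooled model would not be enough, because the categories would hardly overlap in age.

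No new data are needed. The cost is precision: the within-definition age trend has an SE about 2.5 times larger for ages 6–12 than for 6–18, and larger still in the secondary ages. The report should say so, and should not read a non-significant within-stage trend as absence of age dependence.

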### Outcomes

Prior to the start of the investigations in the schools, the German and South African research team will perform a joint training session over several days in Germany to ensure the identical use of the equipment and collection of data. Furthermore, the principal investigator (KH) will attend the first weeks of testing in South Africa to ensure accuracy in methodology and identical data collection. Inter-rater reliability testing will be performed to improve data quality and interpretability.

